### Objectives

The primary objective of this study is to determine if one or more of four new components added to a commercial weight loss programme leads to greater weight loss. The four components to be tested are (1) an introductory video call with the health coach (No vs. Yes), (2) drop-in webchat sessions with the health coach (No vs. Yes), (3) goal setting statements (No vs. Yes), and (4) food diary review and feedback (No vs. Yes). Secondary objectives are to (a) identify which intervention components increase retention and (b) assess whether increased engagement with the programme mediates the association between any observed improvements in weight loss and the four components. The study also aims to explore the fidelity and acceptability of each of the intervention components.

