### Sample size

The available resource allocated to this trial was 48 groups with an average of 30 participants per group. Considering the resource management principle of MOST [7], and given this allocated sample size, we calculated the available power to detect different effect sizes using the R macro %FactorialPowerPlan (Table 5).

**Table 5 Tab5:** Power calculations

**Cohen’s *****d***** effect size**	**Difference in weight**	**Power**
0.25	1 kg	92%
0.22	0.88 kg	85%
0.188	0.75 kg	75%

Power for this study is based on weight change from baseline to 16 weeks. Specifically, the study aims to assess which intervention components contribute to a more than minimal improvement in weight loss to identify components for inclusion in the optimised intervention. Our definition of at least a minimal difference in weight loss is ≥ 0.75 kg—alone or in combination with other components—at 16 weeks. We assumed a standard deviation of 4 kg from previous studies [26], which translates to a component effect size of *d* = 0.188. From a decision-priority perspective, this optimisation trial aims to screen components for an optimised intervention that could be tested in a future definitive evaluation [7, 27]. Therefore, the criteria to consider an effect important will be set liberally at *p*< .10, which is not uncommon for this phase of MOST methodology [8].

Based on previous studies, we assumed a 50% retention rate (an average of 15 participants per group) [26] and a cluster size standard deviation of 5 participants, an intraclass correlation of 0.01 and set alpha to 0.1. This sample size provides 75% power to detect a 0.75 kg difference in weight loss and 92% power to detect any differences of 1 kg or larger. Therefore, this study is powered to detect any main effects or interactions of these sizes or larger.

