#### Primary objective

Data will be analysed using a linear mixed-effect model with repeated measures, to assess whether each component is associated with weight change across the time points (4, 16, and 24 weeks). Participant ID will be added as a random effect, time and component as fixed effects, and an interaction term of component by time. We will also assess two-way interactions between components by adding appropriate multiplicative interaction terms.

The sensitivity of the analysis to assumptions about missing data will be assessed using appropriate methodology that could include (1) last observation carried forward, (2) baseline observation carried forward, and (3) completer analysis. Planned subgroup analyses will categorise participants into three subgroups based on their baseline BMI: (1) participants with a BMI of 21–25 kg/m^2^, (2) participants with overweight (BMI 25–30 kg/m^2^), and (3) participants with obesity (BMI > 30 kg/m^2^). We will also conduct subgroup analyses by age (based on the median age), sex, tertiles of the index of multiple deprivation (with cut points determined from the study population), and presence of pre-diabetes or type 2 diabetes at baseline.

The decision about which components to select for the optimised intervention (i.e., an intervention that includes only active components) will be based on the main effect and interaction estimates obtained from the primary analysis.

Significance levels will be set at *p* ≤ 0.10. Effect sizes and 90% confidence intervals will be reported for all analyses, given the alpha of 0.10. We will also report the more widely used 95% confidence intervals.

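### With about half of the 16-week weights expected to be missing, none of the sensitivity analyses named as examples varies the missing-at-random assumption in a graded way

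*Protocol article*

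**What the plan says.** Under Sample size, the article starts from 48 groups averaging 30 participants and then states: "we assumed a 50% retention rate (an average of 15 participants per group". About 720 of 1440 participants are therefore expected to supply the 16-week weight. The same section sets the decision scale: "Our definition of at least a minimal difference in weight loss is ≥ 0.75 kg", judged at the 10% level.

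Under Primary objective, the analysis is a linear mixed model over weeks 4, 16 and 24. Sensitivity to missing-data assumptions is to be assessed by suitable methods that "could include (1) last observation carried forward, (2) baseline observation carried forward, and (3) completer analysis". No other method is named. Selection of components rests on the main-effect and interaction estimates of the primary analysis.

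Under Objectives, one secondary aim is to "identify which intervention components increase retention". Under Intervention component selection and Intervention components, the components are expected to act partly by raising engagement. The last paragraph of Core intervention reports a possible positive association between engagement and weight loss.

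**The concern.** The mixed model is valid if, given the data in the model, missingness does not depend on the unseen weights. The protocol's own theory gives a reason to doubt this: components may change engagement and retention, engagement may go with weight loss, and engagement is not in the primary model as described. With half the outcome missing, the useful question is how far from MAR the data could be before a selected component no longer looks effective.

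The three named methods do not answer it.

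- **Completers.** This discards the week 4 and week 24 weights of people without a full record, which the mixed model uses. Its assumption is at least as strong as the primary one.
- **BOCF.** It assumes that everyone without a weight lost nothing, and treats that value as observed.
- **LOCF.** It assumes that weight stopped changing at the last reading, and also treats that as observed.

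The last two respond to the share of weights available at each component level as well as to weight itself. Their agreement or disagreement with the primary model could reflect availability alone.

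**Working it through.** **Inputs from the article.** "The available resource allocated to this trial was 48 groups with an average of 30 participants per group"; 50% retention, so 360 analysed per component level; "a cluster size standard deviation of 5 participants, an intraclass correlation of 0.01 and set alpha to 0.1"; "We assumed a standard deviation of 4 kg from previous studies". The test is taken as two-sided because of this sentence: "Effect sizes and 90% confidence intervals will be reported for all analyses, given the alpha of 0.10". The article gives no 16-week mean loss. It gives 7.12 kg at 6 months among those who weighed themselves, so 4 to 7.12 kg is used as an assumed range. The availability gaps are also assumptions.

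**1. The plan's own power.** Coefficient of variation of cluster size = 5/15 = 0.333. Design effect = 1 + ((0.333² + 1) × 15 − 1) × 0.01 = 1.157. SE = 4 × √(2 × 1.157/360) = 0.321 kg. Power at 0.75, 0.88 and 1 kg is 75.6%, 86.4% and 93.0% by the normal approximation, or 74.5%, 85.5% and 92.3% with a t distribution on 46 df. The article states 75%, 85% and 92%, so its figures reproduce.

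**2. BOCF with no effect among those weighed.** Spurious difference = gap in availability × mean loss.

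| Availability | Loss 4 kg | Loss 6 kg | Loss 7.12 kg |
|---|---|---|---|
| 55% vs 50% | 0.20 kg | 0.30 kg | 0.36 kg |
| 60% vs 50% | 0.40 kg | 0.60 kg | 0.71 kg |

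The gap that creates a full 0.75 kg is 0.75/7.12 = 10.5 points to 0.75/4 = 19 points.

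**3. LOCF with no effect among those weighed.** Spurious difference = gap × loss between weeks 4 and 16. If that loss is 3 to 4 kg (assumed), a 10-point gap gives 0.3 to 0.4 kg.

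**4. BOCF with a 0.75 kg effect among those weighed.** At 50% availability in both levels the difference is 0.5 × 0.75 = 0.375 kg. At a 6 kg mean loss, SD = √(0.5 × (16 + 36) − 9) = 4.12 and SE = 2 × 4.12/√1440 × √(1 + 29 × 0.01) = 0.247. Power = Φ(0.375/0.247 − 1.645) = 45%. It runs from 51% to 40% for mean losses of 5 to 7.12 kg. Availability of 43.5% to 45% with the component, against 50% without, removes the difference entirely (0.5 × mean/(mean + 0.75), same range of losses).

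**5. What a graded check would show.** Take a 0.75 kg effect under MAR, half missing at each level, and SE held at 0.321 kg. Suppose missing participants with the component did worse than MAR predicts by delta, and those without did as predicted. The effect is then 0.75 − 0.5 × delta.

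- The 90% CI reaches zero at 1.645 × 0.321 = 0.527 kg, so delta = (0.75 − 0.527)/0.5 = about 0.45 kg.
- The effect reaches zero at delta = 0.75/0.5 = 1.5 kg.
- A shift common to both levels cancels when availability is equal. At 60% vs 50%, a common 1.5 kg shift only moves the effect from 0.75 to 0.75 + 0.1 × 1.5 = 0.90 kg. The shift must therefore be allowed to differ by level.

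**The case against.** The strongest reply is that the list is introduced as examples. The article commits to testing the assumptions, leaves the method open, and may be completed by an analysis plan that is not shown. A reader might infer that only these three methods are permitted. The documents do not support that; they are only the ones named. The point that remains is that the article chose to name methods, and those named suit the stated purpose poorly.

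A reader might also infer that the checks never depart from MAR. That is too strong. BOCF and LOCF do depart from it, each to one fixed point. What is absent is a graded departure around the primary model.

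A third tempting reading concerns decision errors. At a 6 kg mean loss and no weight effect, BOCF would reach p ≤ 0.10 about 34% of the time for a 5-point gap and 78% for a 10-point gap. These are not error rates for choosing components, because selection uses the primary estimates.

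The link from retention to missing weights is inferred. Programme drop-out is defined as cancelling, whereas Weight describes separate prompts, messages and a phone call to obtain readings. Cancellation probably goes with missing weights, but the article does not equate them.

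Finally, if non-weighers truly lost nothing, 0.375 kg would be the correct average, and if retention itself causes weight loss, part of a BOCF difference would be real. Both are fair. They confirm that a BOCF result cannot be interpreted without knowing which assumption holds.

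**Conclusion.** The point holds as a low-cost improvement, not as a fault in the primary analysis. About half of the 16-week weights are expected to be missing, and the methods named cannot say how far from MAR the data must be before a selected component fails. BOCF, and to a lesser degree LOCF, can create or hide a difference close to the 0.75 kg threshold through availability alone.

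The 50% figure is the protocol's own planning assumption. The mean loss at 16 weeks and the size of any availability gap are assumptions of this check. The tipping values of about 0.45 kg and 1.5 kg are illustrations with the SE held fixed.

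**What to change.** In the Primary objective paragraph, replace the list of examples with a named sequence:

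1. Multiple imputation under MAR, with components, baseline and 4-week weight, engagement, cancellation and group in the imputation model.
2. Delta-adjusted imputation of the missing 16-week weights, over a range justified in advance, with delta allowed to differ by component level.
3. For each selected component, the delta at which its 90% CI first includes zero and the delta at which the effect reaches zero.

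Keep BOCF or LOCF at most as supplementary, and report the share of weights available by component level beside them. All the variables are already collected, so the cost is wording and some programming. The one downside is that a delta range must be chosen and defended.

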### Screening, consent, and baseline assessment

Eligibility criteria will be assessed, and baseline data collected, via Second Nature’s bespoke self-reported health questionnaire which will be completed as part of the sign-up process on the Second Nature website prior to commencement of the programme, with no additional instruction. During the questionnaire, participants will be asked to self-report demographic characteristics (date of birth, and sex), anthropometric measures (body weight and height), health-related conditions (diabetes, physical, and mental health conditions), current pregnancy, and their main priorities and goals for the programme. If the participant is ineligible, a pop-up will explain that they do not meet the eligibility criteria for the Second Nature programme, they will not be able to proceed further, and no identifiable information will be collected.

Participants who meet the eligibility criteria will be able to review and accept the Second Nature Terms & Conditions and Privacy Policy, which involves providing consent to be involved in internal and external research and for their data to be used for academic research purposes (Supplementary Material 2). They will then be able to complete the sign-up process, where they can purchase the programme and input their personal contact details (name, email, and home postcode). After sign-up, participants will receive instructions on how to download the Second Nature app. After downloading the app, participants will also be asked to weigh themselves using their weighing scales and record their baseline weight reading in the app.

Participants have the right to withdraw from the programme, and hence also from the trial, and request that all data that has been collected on them is deleted, with no obligation to give a reason.

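### The age (median split) and deprivation (tertile) subgroup analyses discard finer data that are available; for age this costs up to about 11–17 points of power if effect modification is linear

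*Protocol article*

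**What the plan says.** In the protocol article, Statistical Analysis, Primary objective, the planned subgroup analyses include: "We will also conduct subgroup analyses by age (based on the median age), sex, tertiles of the index of multiple deprivation". The deprivation cuts depend on the sample: "tertiles of the index of multiple deprivation (with cut points determined from the study population". No analysis on a continuous scale is mentioned for either variable. The text does not say whether subgroups are compared by an interaction term or analysed as separate strata.

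The section Screening, consent, and baseline assessment shows what is held. The sign-up questionnaire records "demographic characteristics (date of birth, and sex", and at purchase participants "input their personal contact details (name, email, and home postcode". Exact age therefore follows directly. The article does not say how the deprivation index is obtained; the postcode is the evident route. Tertiles cut from the study population already presuppose a finer rank or score.

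The Sample size section states power for component effects on 16-week weight change (Table 5). No power is stated for effect modification by age or deprivation. Component selection is tied to the main-effect and interaction estimates of the primary analysis, not to these subgroups.

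**The concern.** A median split treats two participants just either side of the cut as different and everyone within a half as alike. Unlike the BMI bands, which follow named weight classes, the age and deprivation cuts are given no rationale and will be known only once enrolment is complete. If a component helps increasingly with age, or decreasingly, the split uses only part of that trend.

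Contrasts between subgroups are already much less precise than main effects in this trial. At stake is a lower chance of noticing that a component works differently in older and younger users, from data that are already being collected.

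**Working it through.** **Inputs.** From Sample size: "48 groups with an average of 30 participants per group"; 50% retention, so 15 analysed per group; cluster-size SD 5; SD of weight change 4 kg; and "an intraclass correlation of 0.01 and set alpha to 0.1". The sidedness of alpha is not stated. I take it as two-sided, which reproduces Table 5 and agrees with the analysis section: "Effect sizes and 90% confidence intervals will be reported for all analyses, given the alpha of 0.10". Assumptions not in the documents: effect modification linear in age, age distributed somewhere between uniform and normal, and subgroups compared by an interaction test.

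**Step 1: reproduce Table 5.** Analysed: 48 × 15 = 720, or 360 per level of a component. The coefficient of variation of cluster size is 5/15 = 0.333. Design effect = 1 + ((1 + 0.333²) × 15 − 1) × 0.01 = 1.157. Standard error of a main effect = 4 × √(2 × 1.157/360) = 0.321 kg. Power = Φ(effect/0.321 − 1.645):

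| Effect | Table 5 | Normal approximation | Noncentral t, 46 df |
|---|---|---|---|
| 0.75 kg | 75% | 75.6% | 74.5% |
| 0.88 kg | 85% | 86.4% | 85.5% |
| 1 kg | 92% | 93.0% | 92.3% |

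The plan's figures reproduce, so 0.321 kg is its own precision.

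**Step 2: information kept by the split.** The share kept is the squared correlation between age and its median split, (E|x|/SD)².
- Normal age: 0.798² = 2/π = 0.637.
- Uniform age: 0.866² = 0.75.

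**Step 3: a slope of 0.75 kg per SD of age.**
- Continuous age: z = 0.75/0.321 = 2.34, power 76%.
- Split, normal age: z = 2.34 × 0.798 = 1.87, power 59%, a loss of 17 points.
- Split, uniform age: z = 2.34 × 0.866 = 2.03, power 65%, a loss of 11 points.

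This slope implies a difference in component effect between the age halves of 2 × 0.798 × 0.75 = 1.20 kg (normal) or 2 × 0.866 × 0.75 = 1.30 kg (uniform).

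**Step 4: the same by difference between halves.** Each half has 360 participants, so the standard error of the difference is 2 × 0.321 = 0.641 kg. The z for the split is D/0.641; the z for continuous age is that value divided by 0.866 or 0.798.

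| Difference D between halves | Split | Continuous (uniform to normal) | Loss, points |
|---|---|---|---|
| 0.75 kg | 32% | 38–43% | 7–11 |
| 1.0 kg | 47% | 56–62% | 10–16 |
| 1.25 kg | 62% | 73–79% | 11–17 |
| 1.5 kg | 76% | 86–90% | 10–15 |
| 2.0 kg | 93% | 98–99% | 5–6 |

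The loss peaks where continuous age has about 75–80% power.

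**Step 5: check with clustering.** A simulation of 48 groups (mean size 15, SD 5, ICC 0.01) gave losses of 8–12 points at 0.75 kg, 11–16 at 1 kg and 9–12 at 1.5 kg. Groups are formed partly by age. With normal age half determined at group level, the loss at 1 kg was 16.5 points.

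**Step 6: deprivation is a separate calculation.** At 75–80% reference power, tertiles lose about 4–9 points if tested as a trend score and about 13–18 points on a 2-df test. The article does not say which would be used.

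**The case against.** The strongest reply is that nothing decided by the trial depends on these analyses. Components are chosen on the primary analysis, and no subgroup power is claimed. That stands, and it sets the grade of the point.

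Second, a reader might infer that the split costs 11–17 points whatever the truth. The documents do not support that. They give no age distribution, no expected modification and no reference power. The range needs a linear trend and a difference of about 1.2–1.3 kg between halves, well above the protocol's 0.75 kg minimal effect. At 0.75 kg power is low either way, and continuous age does not rescue the question. Groups are formed as mostly older, mostly younger or mixed, so a step-like pattern is conceivable; a step near the median would cost the split nothing.

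Third, a reader might carry the age figure over to deprivation. Tertiles lose a different amount, which depends on the test used.

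Fourth, a reader might infer that sample-based cuts cannot be used again in a later definitive trial. They can: the observed median and tertile values can be reported and reapplied. Fixing the rule in advance also guards against choosing cuts to suit the result.

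Finally, it can be said that model detail belongs in an analysis plan not shown here. That would answer a silence, but the article states the median and tertile method outright. What remains is the loss of information under a roughly linear trend.

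**Conclusion.** The point holds as a minor one. The article commits to coarser age and deprivation groupings than its data require. For age, under linear modification and a distribution between uniform and normal, the split keeps about 64–75% of the information. The cost is up to about 11–17 points of power at two-sided alpha 0.10, and about 7–11 points when the component effect differs by 0.75 kg between age halves. These figures rest on the plan's own SD, ICC, retention and cluster sizes, and on an interaction test that the article does not specify. They say nothing against the primary analysis, the stated power in Table 5 or the rule for selecting components.

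**What to change.** Test effect modification at week 16 with component-by-age and component-by-deprivation interaction terms in the primary model, with age in years and deprivation as a rank or score. Check linearity with a plot or spline. Keep the median-split and tertile estimates for display, and report the numerical cut points used.

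The cost is about one sentence of analysis wording, settled before outcome data are analysed, and no new data collection. Because the data are anonymised before transfer to the researchers, the transferred file should carry age in years and the deprivation rank or score, not only the categories. The downside is that the test assumes a linear form and would be less suited to a sharp step; the plot or spline and the retained categories would show that.

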#### Secondary objectives

For the secondary outcome, the proportion of participants that drop-out from baseline to 4, 16, and 24 weeks will be assessed using logistic regression analyses.

We will also explore whether engagement acts as a mediator in the association between components and weight change. Mediation effects will also be tested for significance using the general approach described previously [28]. Engagement will be considered as a mediator if engagement significantly predicts weight and if the group effect is attenuated with adjustment for the engagement variable. The indirect effect and proportion of total effect mediated will also be calculated.

#### Process evaluation

Descriptive statistics will be used to summarise the quantitative intervention component fidelity measures. Descriptive statistics will also be calculated for the individual items on the acceptability questionnaire and overall, for each intervention component.

### Data management

Second Nature will be the data owner and controller. Data collected at assessment timepoints throughout the trial will be stored on their secure servers with trusted 3rd party suppliers, compliant with the United Kingdom General Data Protection Regulation. All identifiable information, which will be provided by the participant to Second Nature, is governed by their privacy policy. Data will be anonymised by Second Nature after study completion and transferred to the researchers at Oxford via a secure University information governance approved method for data transfer. The dataset will be stored on a University secure server with access held by the study team. Within the University server, all data will be stored in password protected folders, accessible only to members of the research team.

